#### Analysis data sets

Full Analysis Set (FAS)—All randomised patients who received at least one dose of ME or placebo will be included in the statistical analyses of primary and secondary endpoints. FAS is equivalent to an ITT analysis set, as all participants will take their first injection with the study drug at baseline visit. To be included in the analysis of the secondary endpoints, a baseline value and at least one post baseline assessment is required. Patients will be included in the treatment groups according to randomisation. Patients lost to follow-up or withdrawing consent from the trial will be censored for the primary analysis and will not be replaced.Per Protocol (PP) analysis set—A per protocol analysis will be performed for OS as a sensitivity analysis. This analysis will exclude any patient who has at least one significant protocol deviation believed to have a potential impact on the efficacy outcome (OS), e.g. patients who received the wrong treatment, not enough treatment, or patients receiving prohibited therapy. Decisions regarding major protocol deviation will be made before unblinding the trial.Safety Analysis Set (SAS)—All randomised patients who received at least one dose of ME or placebo will be included in the statistical analyses of primary and secondary endpoints. Patients will be included in the treatment groups according to treatment actually given. SAS represents a PP analysis set including all participants that have started treatment.

### Interim analyses {21b}

No interim analysis will be performed.

### Methods for additional analyses (e.g. subgroup analyses) {20b}

Subgroup analyses will be performed regarding possible confounders such as prior and concurrent cytotoxic treatment, performance status and concomitant medication for symptom relief.

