### Objectives {7}

The overall objective of the present trial with two ancillary studies is to assess the value of ME as a complement to standard treatment in advanced pancreatic cancer.

The primary objective is to compare overall survival (OS) in patients with advanced pancreatic cancer randomised to either ME or placebo.

The secondary objectives are to compare health-related quality of life (HRQoL), body weight, corticosteroid use, adverse events (AE) and costs for supportive care and inpatient care.

Ancillary studies

Two ancillary studies aim to
Assess immunological effects and to explore potential prognostic and predictive biomarkers (biomarker study).Explore advanced pancreatic cancer patients’ experiences of every-day life (qualitative study)

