### Relevant concomitant care permitted or prohibited during the trial {11d}

Through the Swedish health care system, participants have access to palliative supportive care, either as in- or outpatient care, for symptom relief and psychological and social support.

Initiation or termination of or switch to a new line of palliative chemotherapy does not affect the patients’ participation in the trial. Palliative radiotherapy is permitted.

As no drug-drug interactions with ME are known, all drugs, except those mentioned in exclusion criteria, are allowed. Each drug given during study participation is regarded as concomitant medication and is registered in the electronic case report form (eCRF), including complementary compounds such as nutritional supplements, vitamins, natural remedies and homoeopathic drugs.

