#### Secondary outcomes

We will measure generic and disease-specific aspects of *HRQoL* using the following validated questionnaires at baseline, 6 weeks and 2, 3, 4, 6 and 9 months after randomisation:
EORTC QLQ-C30 [54], a generic questionnaire developed to assess HRQoL of patients with cancerEORTC QLQ-PAN26 [55], a questionnaire developed to assess the HRQoL for patients with pancreatic cancer

*Body weight* will be assessed at every visit and participants will also report weekly weight measures via the study-specific patient diary.

*Corticosteroid use* is assessed by recording concomitant medication at every visit.

*Adverse events* will be assessed at every scheduled visit, via telephone contact and at unscheduled visits.

Data for calculation of *observed costs* for supportive care and inpatient care will be collected at every visit by assessment of concomitant medication and days in hospital since previous visit. In addition, study-specific patient diaries provide information on need of total parenteral nutrition, visits from the palliative home care team and consumption of dietitian-prescribed nutritional supplement drinks.

*Baseline information* on diagnosis, such as imaging, histology, tumour classification and potential previous treatment such as surgery and chemotherapy for participants with relapse, will be collected from participants’ medical records. Medical history is taken at baseline visit. Data from telephone contacts and unscheduled visits will be collected continuously.

Data on ECOG *performance status*, *physical examination*, *concomitant medication*, *access to* (and if needed referral to) *palliative home care team*, *body weight* (and *height* at baseline visit), *spontaneously reported local reactions* and *side effects* will be collected at each study visit. The ECOG scale is used for scoring of performance status. The numbering scale from 0 (fully active) to 4 (completely disabled) helps to assess the functional status of a patient in terms of their ability to care for themselves, daily activity and physical ability (walking, working, etc.).

*Drug account*, *compliance* and *changes or interruptions in study treatment* will be collected from study-specific patient diaries covering the time between study visits and if necessary, completed by inquiry of the participant or their next of kin.

Ancillary studies

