Generally, trials in oncology are often difficult to blind, since the active treatment, e.g. chemotherapy or immunotherapy, confers obvious adverse events and complications which would not occur in a placebo arm. To date, there is no placebo capable of exactly mimicking the possible local reactions such as they might occur from ME at higher dosages without conferring a risk of toxicity. Local reactions have been shown to be more common in females, younger patients, during chemotherapy and in patients with lower tumour stage [48]. Our study population consists of patients of both sexes in advanced tumour stage and many participants being treated with chemotherapy. Subcutaneous injections in general may cause non-specific local redness immediately after injection. While the patients receive general information about local redness following any type of subcutaneous injection, no specific remarks are made on potential local reactions specific to ME. We therefore expect successful blinding in all control patients and in most patients of the treatment arm. Nevertheless, all reported local reactions and local overreactions are documented systematically to enable an estimation of potential unblinding. In any case, a significant effect on OS by expecting just another medication in such a severe disease as advanced pancreatic cancer is highly unlikely [68]. Even regarding HRQoL, expectation effects are questionable in cancer patients [69].

Two more effective chemotherapy combinations (gemcitabine/nab-paclitaxel and FOLFIRINOX) have been introduced at about the same time as trial start, resulting in longer OS (about 8 months instead of 5 months) for a smaller group of highly selected patients eligible for these treatments. We chose not to modify the study protocol and insert another stratum apart from the original chemotherapy/no chemotherapy stratification. In the unlikely event of unequal distribution of this variable, this will be accounted for through regression analysis.

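### Subgroups on concurrent chemotherapy and symptom medication, called possible confounders, take in post-randomisation treatment and can bias the mistletoe effect within them

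*Protocol article*

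**What the plan says.** Under Methods for additional analyses {20b} the protocol article says: "Subgroup analyses will be performed regarding possible confounders such as prior and concurrent cytotoxic treatment, performance status and concomitant medication for symptom relief". No time point is given for any of these variables.

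Two statements under Relevant concomitant care {11d} show what two of them contain. On medication: "Each drug given during study participation is regarded as concomitant medication". On chemotherapy: "Initiation or termination of or switch to a new line of palliative chemotherapy does not affect" a patient's participation.

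The secondary objectives under Objectives {7} include "body weight, corticosteroid use, adverse events (AE) and costs for supportive care and inpatient care". Under Secondary outcomes, corticosteroid use "is assessed by recording concomitant medication at every visit". The same section says that performance status and concomitant medication "will be collected at each study visit", so both baseline and later values exist.

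The Discussion notes that two newer chemotherapy combinations came into use at about the time the trial started, and that no further stratum was added for them. It then says: "In the unlikely event of unequal distribution of this variable, this will be accounted for through regression analysis".

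**The concern.** A confounder of a treatment comparison is a common cause of treatment and outcome. Allocation here is random, so a drug started after allocation cannot be one. It can only follow from the allocation, from the course of the disease, or from both. Splitting patients on it compares groups that randomisation no longer balances.

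Two routes lead to bias. First, ME may change the variable. The trial tests fatigue, appetite loss and corticosteroid use as outcomes, and each of these could move symptom medication. Second, ME may change survival. A patient who lives longer has more time to start a drug or a new line of chemotherapy, so ever-use differs by arm even if ME has no direct effect on prescribing.

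Corticosteroids show the inconsistency most clearly. As far as they count as symptom relief, one medication record serves both as an outcome that ME might change and as a variable used to form groups. At stake is whether the subgroup hazard ratios can be read as treatment effects.

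**Working it through.** **Timing of each variable, from the article's own text**

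| Variable in {20b} | Timing |
|---|---|
| Prior cytotoxic treatment | Before randomisation; sound |
| Performance status | Recorded at every visit; sound if the baseline value is used |
| Concurrent cytotoxic treatment | Set against prior treatment; may start, stop or switch on study |
| Concomitant symptom medication | Any drug given during participation |

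The last two are at least partly post-randomisation.

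**Size.** The plan gives no figure on this point, so there is none to reproduce. The following is an illustration for a symptom drug only; chemotherapy was not simulated.

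From the article: 1:1 allocation and a 9-month treatment period. Assumed: exponential survival with a control median of 6 months (death rate λD = ln 2 / 6 = 0.1155 per month), drug start rate λM = 0.15 per month, and no censoring of deaths. A user is a patient who starts the drug before death and before month 9. A shared normal frailty (SD 0, 0.7 or 1.0 on the log-hazard scale) raises both rates. Each scenario has 400,000 patients, analysed with a Cox model.

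Check on the share of users without frailty: P(user) = λM/(λM+λD) × [1 − exp(−9(λM+λD))].
- Placebo: 0.15/0.2655 × [1 − exp(−2.390)] = 0.565 × 0.908 = 0.51.
- ME halving the start rate: 0.075/0.1905 × [1 − exp(−1.715)] = 0.394 × 0.820 = 0.32.

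Both agree with the simulation.

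Results with **no true effect on survival** (correct HR 1.00):

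| Frailty SD | ME effect on drug start | Users, placebo / ME | HR non-users | HR users | HR adjusted for ever-use |
|---|---|---|---|---|---|
| 0 | 1.0 | 51% / 52% | 1.002 | 1.005 | 1.003 |
| 0 | 0.67 | 51% / 40% | 0.873 | 0.977 | 0.909 |
| 0 | 0.5 | 51% / 32% | 0.812 | 0.955 | 0.857 |
| 0 | 1.5 | 51% / 63% | 1.228 | 1.028 | 1.131 |
| 0.7 | 0.67 | 48% / 38% | 0.951 | 0.997 | 0.968 |
| 0.7 | 0.5 | 48% / 31% | 0.928 | 1.002 | 0.953 |
| 0.7 | 1.5 | 48% / 60% | 1.079 | 1.011 | 1.044 |
| 1.0 | 0.67 | 46% / 36% | 0.993 | 0.997 | 0.996 |
| 1.0 | 0.5 | 46% / 30% | 0.975 | 1.006 | 0.986 |
| 1.0 | 1.5 | 46% / 57% | 1.028 | 0.983 | 1.006 |

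Subgroups fixed at baseline in the same null runs gave HRs of 0.99 to 1.01 throughout.

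The mechanism is that many non-users are patients who died before they could start the drug. The faster the drug is started in an arm, the more its non-users are weighted towards early death. Shared frailty pulls the other way, because sicker patients start sooner and leave the non-user group, so the two distortions partly cancel.

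With a **true HR of 0.67** (the planning value under Sample size), no frailty and no effect of ME on prescribing, use still differs. In the ME arm λD = 0.0774, so P(user) = 0.15/0.2274 × [1 − exp(−2.047)] = 0.660 × 0.871 = 0.57, against 0.51 on placebo. The non-user HR is 0.71. If ME also raises drug start by a factor of 1.5, the non-user HR is 0.90.

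For scale at 145 per arm, if all die, take the null case with drug start halved. Without frailty there are about 145 × 0.49 = 71 placebo and 145 × 0.68 = 99 ME non-users. The SE of the log HR is about √(1/71 + 1/99) = 0.156, and ln 0.812 = −0.208, a shift of about 1.3 SE. With frailty SD 0.7 (about 75 and 100 non-users) the SE is 0.153 and ln 0.928 = −0.075, about 0.5 SE.

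**The case against.** The additional-analyses section fixes no time point, subgroup definitions are commonly left to an analysis plan, and the article promises one before unblinding. Baseline values exist for performance status and medication, and concurrent chemotherapy might partly mean the eligibility stratum. This stands in part: an analysis plan could still restrict these variables to baseline. But the article already names the variables, sets concurrent against prior treatment, defines concomitant medication as what is given on study, and gives confounding as the reason. Followed as written, it leads to post-randomisation subgroups.

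The size is driven by assumptions, covers one kind of variable, and can be negligible. That stands. Where ME changed neither drug use nor survival there was no bias, and with frailty SD 1.0 it was at most about 3% under the null. The claim is that such subgroups can mislead, not that they must.

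A reader might also infer that the Discussion's regression adjusts for a post-randomisation confounder. The text does not support that. It speaks of patients eligible for the newer combinations, beside a stratum that was considered and not added, and never calls regimen a confounder. It can be read as correction of a chance baseline imbalance. What remains is an unstated time point and a model chosen after looking at the data.

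Nor does the article say that these subgroups will be used to claim that ME works with or without chemotherapy. And listing corticosteroid use as a two-sided secondary comparison is not a statement that ME is expected to change it.

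**Conclusion.** The concern holds for subgroups on concurrent cytotoxic treatment and concomitant symptom medication. As described, they can include treatment begun after randomisation, they are wrongly called confounders, and one likely component, corticosteroids, is also an endpoint. Prior cytotoxic treatment, and performance status if taken at baseline, are legitimate.

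Under a true null, the illustrative non-user HR runs from about 1.0 to 0.81 or 1.23. The extremes need no shared frailty and a sizeable effect of ME on drug start (HR 0.5 or 1.5); with frailty SD 0.7 the range is 0.93 to 1.08. The control median, drug start rate, frailty and ME effect on prescribing are all assumed.

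The reach is limited to additional analyses. It would be wrong to infer that the primary log-rank test is compromised, since it does not use these subgroups. The if-unequal rule for combination chemotherapy is a lesser fault: a data-dependent choice with no stated time point.

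**What to change.** In the protocol or analysis plan, before unblinding:

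- Define every subgroup variable by its value at or before randomisation: chemotherapy eligibility stratum, prior cytotoxic treatment, baseline ECOG status, and baseline symptom medication including corticosteroids.
- Drop the word confounders.
- Report treatment-by-subgroup interactions with confidence intervals, labelled exploratory.
- Report on-study chemotherapy and symptom drugs by arm, descriptively or as outcomes.
- Replace the if-unequal rule in the Discussion with one pre-specified sensitivity model that uses the regimen planned at randomisation, where that is recorded.

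The cost is mainly wording. The stratum is held in the randomisation system, and the article lists performance status, concomitant medication and previous treatment of relapsed patients among the data collected. It does not list the planned regimen among the baseline items, and recruitment opened in June 2016, so its availability must be checked first. The small downside is that on-study treatment patterns are no longer used as effect-modifier subgroups.

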### Methods in analysis to handle protocol non-adherence and any statistical methods to handle missing data {20c}

Patients lost to follow-up or withdrawing consent from the trial will be censored at end of treatment and will not be replaced. We follow EORTC’s recommendations on calculation and handling of missing data [61] in HRQoL questionnaires. We do not plan to use imputation when reporting HRQoL data.

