#### Termination of trial intervention

Study treatment is terminated after 9 months from the baseline visit. Treatment may be terminated earlier due to the participant’s own decision to withdraw consent or in case of medical, psychiatric, cognitive or other conditions occurring that may endanger the patient’s ability to comply with study protocol or complete the trial. Other reasons for early treatment termination are serious adverse events with suspected causal relationship to the study drug (such as allergic reaction CTCAE Grade ≥ 2, anaphylaxis, erythema multiforme or other events which may cause severe or permanent harm), or major violation of study protocol. The treatment might also be stopped in the very late palliative stage, if a potentially life-extending effect is no longer considered desirable.

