### Outcomes {12}

Primary endpoint for the trial is OS defined as time from randomisation to death of any cause.

Secondary endpoints are HRQoL measured by the European Organisation for Research and Treatment of Cancer (EORTC) HRQoL questionnaires QLQ-C30 [54] and QLQ-PAN-26 [55] at study visits (baseline, 5–6 weeks, 2, 3, 4, 6 and 9 months after randomisation), body weight (documented weekly in patients’ study-specific diaries and at abovementioned study visits), corticosteroid use (continually from participants’ health records from baseline visit to end of study participation), adverse events (assessed at abovementioned study visits and continually from health records from baseline visit to end of study participation), costs for supportive care and costs for inpatient care (calculated from documentation in study-specific patient diaries and continually from health records from baseline visit to end of study participation).

OS as primary endpoint and HRQoL as secondary endpoints are chosen due to their high clinical relevance in pancreatic cancer patients, reflected by the fact that all palliative oncological treatment in this patient group aims to both improve HRQoL and to prolong survival, if possible.

Ancillary studies
Endpoints include analyses of blood cell count, differential, leukocyte subtypes, CRP, CA 19-9, albumin, anti-mistletoe lectin antibodies, IgG subtypes and cytokines at baseline and under follow-up. Whole blood is collected at baseline for isolation of DNA from peripheral leukocytes and subsequent analyses of DNA sequence and variations.The outcome of the qualitative study is to understand participants’ every-day life situations, symptom burden and management, self-administration of subcutaneous injections and experiences of participating in a randomised placebo-controlled trial on ME.

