## Data collection and management

### Plans for assessment and collection of outcomes {18a}

#### Primary outcome

Overall survival is primary outcome. 

After all included participants have fulfilled their treatment period (*n* = 290), survival status and eventual date of death will be checked for all participants at the Swedish Tax Agency’s register covering all inhabitants in Sweden and updated on a daily basis.

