## Statistical methods

### Statistical methods for primary and secondary outcomes {20a}

All results will be reported according to the Consolidated Standards of Reporting Trials Guidelines, including the extension for patient-reported outcomes [59, 60].

In general, all endpoints, demographic and baseline data will be summarised using descriptive statistics and graphs as appropriate. Continuous variables will be summarised by descriptive statistics (number of patients (*n*), mean, standard deviation (SD), minimum, median and maximum). Categorical variables will be summarised in frequency tables (frequencies and percentages). Statistical tests used to compare between treatment groups will be done two-sided at a significance level of 5%, unless otherwise stated. In addition to *p* values, point estimates and corresponding 95% confidence intervals (CI) will be presented. A separate Statistical Analysis Plan will be written before unblinding the trial, giving more detailed information about the statistical analyses.

Primary endpoint is overall survival time. Overall survival time is defined as the time from date of randomisation until death. Any patient not known to have died at the time of analysis will be censored based on the last recorded date on which the patient was known to be alive, i.e. their status must be known on the censored date and should not be lost to follow-up or unknown.

A log rank test will be performed for the primary analysis of OS time. The following hypothesis will be tested:
H0: no difference between ME and placeboH1: difference between ME and placebo

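### The protocol gives two incompatible censoring rules for overall survival, and one of them would drop register-known deaths in patients who are lost or withdraw consent

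*Protocol article*

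**What the plan says.** Four places in the protocol article bear on who counts as a death in the primary analysis.

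- Outcomes {12} sets the endpoint: "OS defined as time from randomisation to death of any cause".
- Plans for assessment and collection of outcomes {18a}, Primary outcome, sets the data source. Once all participants have completed the treatment period, "survival status and eventual date of death will be checked for all participants" in a register "covering all inhabitants in Sweden and updated on a daily basis".
- Statistical methods {20a} sets one censoring rule: "Any patient not known to have died at the time of analysis will be censored based on the last recorded date" of known survival. It adds that status must be known on that date.
- Analysis data sets and {20c} set another. The first says: "Patients lost to follow-up or withdrawing consent from the trial will be censored for the primary analysis and will not be replaced", without a date. The second supplies the date: "Patients lost to follow-up or withdrawing consent from the trial will be censored at end of treatment and will not be replaced".

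The full analysis set is described as equivalent to an intention-to-treat set. Under {11b}, study treatment ends at 9 months or earlier, and withdrawal of consent is one of several listed reasons for ending early.

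**The concern.** The rules in {18a} and {20a} make death status depend on what the register shows. The rule in Analysis data sets and {20c} makes it depend on whether the patient stayed in the trial. For patients who leave and then die, these give different event indicators and different times, so one protocol defines two primary datasets.

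The second rule is the harder one to defend. Missing clinic visits is no reason to censor OS when vital status comes from a population register. Dropping deaths that are already known also conflicts with an analysis set presented as intention-to-treat. What is at stake is the event count behind the stated power and, under less certain conditions, the hazard ratio (HR) itself. If the conflict is still open when results are seen, there is also a choice between two datasets.

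**Working it through.** **1. The rules applied to one patient.** A patient withdraws consent at month 3, takes the last injection then, and dies at month 4 according to the register.

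| Rule | Time | Status |
|---|---|---|
| {18a} with {20a} | 4 months | death |
| Analysis data sets with {20c}, end of treatment = last dose | 3 months | censored |
| Analysis data sets with {20c}, end of treatment = planned month 9 | 9 months | censored |

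The term end of treatment is not defined for this purpose. On the last reading the patient is even credited with five months of survival after death. No reading of {20c} gives the result of {18a} with {20a}.

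**2. The plan's own power figure.** Inputs from Sample size {14}: HR 0.67, two-sided 5% level, 90% power, 145 per arm. Schoenfeld's formula for equal allocation is

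d = 4 (z₀.₉₇₅ + z₀.₉₀)² / (ln HR)² = 4 × (1.960 + 1.282)² / (−0.4005)² = 4 × 10.507 / 0.1604 = 262.1, so 263 deaths.

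Freedman's formula gives 10.507 × (1.67/0.33)² = 269.1, so 270 deaths. These are 263/290 = 90.7% and 270/290 = 93.1% of the sample. The stated 90% is reproduced if about 91 to 93% of participants are observed to die. The protocol gives no event number, so that share is implied.

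**3. Losing deaths.** Power = Φ(√d/2 × |ln HR| − 1.960). The shares lost are assumptions.

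| Share of 263 deaths lost | Deaths left | Power |
|---|---|---|
| 0% | 263 | 90.1% |
| 5% | 249.9 | 88.6% |
| 10% | 236.7 | 86.9% |
| 15% | 223.6 | 84.9% |

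If all 290 had died (power 92.6%), losing 10% would leave 261 deaths and 89.9% power.

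**4. Bias in the HR.** Simulation, 3,000 trials per scenario. Assumptions, none from the protocol's analysis plan: exponential survival, placebo median 6 months, follow-up uniform between 9 and 60 months, and withdrawal falling within the 2 months before death and before month 9. The test is an unstratified log-rank test. Percentages are the chance that a patient is of the withdrawing type; the share of all patients actually censored by the rule is 6 to 12% in these rows.

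| True HR | Withdrawal, placebo / mistletoe | Estimated HR | Rejection rate |
|---|---|---|---|
| 0.67 | 10% / 10% | 0.67 | 88% |
| 0.67 | 20% / 20% | 0.67 | 86% |
| 0.67 | 10% / 20% | 0.62 | 95% |
| 0.67 | 20% / 10% | 0.72 | 72% |
| 1.00 | 10% / 20% | 0.93 | 9% |
| 1.00 | 20% / 10% | 1.08 | 9% |

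Counting the register deaths instead gives HR 0.67 with about 90% power, or HR 1.00 with about 5% type I error, in every row.

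**5. Relaxing each condition.** Keep 10% against 20% but spread withdrawal evenly over the 9 treatment months: the HR stays at 0.67 or 1.00 and type I error at 5 to 6%. Keep withdrawal tied to death but make it 5% against 7%: the null HR is 0.99 or 1.01 and type I error about 5%. Material bias needs both conditions together.

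**The case against.** The best defence is that {20a} is the method section for the primary endpoint and can be read as governing. On that reading, the sentences in Analysis data sets and {20c} apply only where the register gives no status or the patient refuses further follow-up. The {20c} sentence does not name OS. Loss to follow-up may also be rare, since {18b} allows home visits or phone calls for patients too ill to attend, and earlier censoring is legitimate for someone who refuses all further use of data. A separate analysis plan, to be written before unblinding, may settle the matter.

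Much of this stands. It means that the discarding of deaths is one of two stated rules and not a settled plan, and that the affected group may be small. It does not remove the conflict: Analysis data sets ties the censoring to the primary analysis, and neither sentence is limited to patients without register status. An analysis plan would first have to choose between the two rules.

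A reader might also infer that everyone who stops injections is censored, because {11b} says that "The treatment might also be stopped in the very late palliative stage". The documents do not support this. The censoring sentences cover only patients lost to follow-up or withdrawing consent, and a late palliative stop of treatment is neither. Nor does {11b} say that deterioration is the main reason for stopping; it lists several.

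**Conclusion.** The protocol contradicts itself on the censoring of its primary endpoint, and this should be resolved before unblinding. If the rule in Analysis data sets and {20c} is followed, register-known deaths are dropped in patients who are lost or withdraw consent. With about 263 of 290 deaths needed there is little slack: an assumed loss of 5 to 15% of deaths brings power from 90% to about 89 to 85%.

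It would be too strong to say that the HR will be biased or the type I error inflated. That requires withdrawal related to prognosis and clearly unequal between arms. Some imbalance is conceivable, since the Discussion accepts that the placebo cannot exactly mimic local reactions to mistletoe, but its size and direction are unknown and the documents give no withdrawal rates. The null HR of 0.93 or 1.08 with about 9% type I error is a stress case. With equal withdrawal the cost was a few points of power and no bias.

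It would also be too strong to say that the register holds every death. It covers inhabitants of Sweden, so emigrants could be missed, and a participant may refuse register follow-up.

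**What to change.** State one OS rule and use it in {20a}, Analysis data sets and {20c}:

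- Remove censoring at end of treatment for OS.
- Count every death in the register up to one common extraction date, regardless of treatment stop, loss to visits or withdrawal from study procedures.
- Censor survivors at that extraction date.
- Censor earlier only for emigration, or at the date of express withdrawal of consent to register follow-up. Report the number of such patients by arm.

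The cost is a sentence or two in the protocol and the analysis plan. The register look-up for all participants is already planned, so no new data collection is needed. The change should be made before unblinding.
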